### General data collection and follow up

After receiving informed consent a questionnaire will be filled out with patient characteristics and the pre-fracture status of the patient. Information about the status before the fracture will be gathered using the 10-item modified Barthel Index for ADL-functioning [42], the Parker and Palmer pre-fracture mobility score [43], the Short Nutritional Assessment Questionnaire [44] and the Delirium Observation Screening Scale [45]. In addition, information will be gathered about the home situation before admission. Before discharge, the questionnaire will be completed with information about the occurrence of pressure wounds, delirium, urinary tract infections, wound infections, falls during admission and possible risk factors after discharge for these complications.

All included patients will be followed for a period of six months after discharge. During this period two interviews by telephone will be held with all included patients, two weeks and six months after discharge. During these interviews patients will be asked some multiple choice questions about their current residence, physical functioning, use of health care, the occurrence of unexpected events and some open end questions about their experiences during the whole care process. In addition to these interviews, the retrospective patient record review study will be conducted to review the patient record up to six months after discharge. The methods of this record review study will be identical to the baseline measurement described earlier. Again, the reviewers will look for complications, adverse events, the quality of record keeping and written information for the transfers of the patient between the different hospital wards. This second record review study will be used to assess the effect of the complete intervention programme on the possible reduction in complications and adverse events.

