### Participating surgical wards

Because the researchers will frequently have to visit the participating surgical wards during the study, one hospital region in the Netherlands will be chosen for the recruitment. Although the treatment for hip fractures is fairly standardised by means of protocols, we aim to include a surgical ward of each of the three hospital types that exist in the Netherlands; a university, a tertiary medical teaching and a general hospital. A fourth surgical ward in another hospital will be included as a control group. An inclusion criterion for the surgical wards is that they have to treat at least 100 elderly patients with a hip fracture each year. The wards will be recruited by informing already existing contacts within the wards about the study. If the ward agrees to participate an official intake by the researchers will follow. The nurses in the participating wards will be informed about the study during a meeting. In this meeting the interventions and the inclusion process will be explained. For each ward background information will be gathered about the number of patients, treatment procedures and discharge planning. This will make it possible to compare the wards and correct for important differences.

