#### Method

The incidence of complications and AEs will be measured within the care chain and especially during the hospital admission of elderly hip fracture patients. In this study we look at the care chain from the moment that the patient is brought into the emergency department until six months after discharge from the hospital. Therefore the patients' hospital record will be studied in retrospect by an experienced surgeon. For the baseline measurement patient records of hip fracture patients acutely admitted in 2007, the year previous to the start of the intervention study, will be reviewed using a structured review form. In each hospital all surgical and orthopaedic admissions of patients with a hip fracture of 65 years or older will be selected. Of these selected index admissions the medical, nursing and, if existing, the outpatient records will be collected, the X-rays made during the admission will also be available. Records of patients with a pathological fracture, polytrauma or elective admission will be excluded. The main outcome variables in this part of the study are: rate of complications, adverse events, near misses and information transfer between care providers.

The patient records will be reviewed by a team of eight experienced reviewers. The selection criteria for the reviewers are:

• At least ten years post graduate clinical (surgical) experience;

• Surgical experience with hip fractures;

• Good reputation among colleagues;

• No longer than 8 years retired at the start of the study;

• Experience or affinity with analysis of incidents, complaints and errors.

Most of the reviewers have participated in a previous record review study [39] and therefore are already familiar with this type of research, terminology and methodology. Nevertheless, they will all follow a half-day training led by the research team and one experienced reviewer. During this training, the definitions, study protocol, adjusted review form and examples of AEs will be discussed. The reviewers will also receive a review manual. They will be compensated for their review activities at an hourly rate for expenses. During the review process the reviewers can ask advice from a general internist about accepted clinical practice in the specialty of internal medicine.

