##### Evaluation

The implementation and effectiveness of the patient safety card will be established during an interview by telephone with the patient two weeks after discharge. We will consider the patient safety card successful when 60% of the patients has used the card and found it useful. One of the topics in the interview is therefore about the use and possible added value of the patient safety card and the need and possibility for patients and their family to get actively involved. Also, the possible consequences of the use of the patient safety card on the patients' trust in health care are discussed during these interviews. Finally, during the retrospective patient record review six months after discharge the number of complications and adverse events will be determined and compared to the baseline measurement.

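### Trial complications are compared with 2007 records although the two periods differ in who is counted and how events reach the record, and the control hospital's own change is not netted off

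*Protocol article*

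**What the plan says.** **The comparison with 2007.** Under Baseline measurement, Method, the source is fixed: "patient records of hip fracture patients acutely admitted in 2007, the year previous to the start of the intervention study, will be reviewed". The baseline Aim calls this information the starting point for evaluating the intervention study. For the patient safety card (Intervention B, Evaluation), "the number of complications and adverse events will be determined and compared to the baseline measurement". General data collection and follow up adds a sentence on the programme as a whole, cut here before its last word: "This second record review study will be used to assess the effect of the complete intervention programme on the possible reduction in complications and adverse". That last sentence does not name its comparator.

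**Data collection in the trial only.** The same section says: "After receiving informed consent a questionnaire will be filled out with patient characteristics and the pre-fracture status of the patient". The listed instruments include a nutrition questionnaire and a delirium observation scale. Later, "Before discharge, the questionnaire will be completed with information about the occurrence of pressure wounds, delirium, urinary tract infections, wound infections, falls during admission". The section describes the second record review as using the same methods as the first.

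**Who is in each period.** For 2007: "In each hospital all surgical and orthopaedic admissions of patients with a hip fracture of 65 years or older will be selected", with pathological fracture, polytrauma and elective admission excluded. The trial criteria (Participants) also require planned surgery, good cognitive condition and informed consent.

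**The concurrent control.** Study design also plans a comparison with usual care, and the Power calculation provides a control group of 80. No section sets the intervention wards' change since 2007 against the control ward's change.

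**The concern.** A before-after contrast takes in everything that changed between the two periods, not only the programme. Two such changes are built into this plan.

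- **Recording.** A trial form that asks about delirium, pressure wounds, infections and falls can lead ward staff to notice, treat and chart events that would have gone unrecorded in 2007. The Definitions count a complication when it requires an adjustment of treatment, so an event that is noticed and then treated can qualify wherever the form itself is kept. Identical review methods standardise how records are read, not how they came about.
- **Case mix.** The 2007 records include patients whom the trial excludes for poor cognition or who would not have consented. The limitations section itself says that leaving out patients with dementia may understate the problems experienced. It does not apply this to the comparison with 2007.

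Complications are a primary outcome, and the planned effect is only 5 points. A before-after difference of that order could be wrongly credited to the card or the programme, or a real benefit could be hidden.

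**Working it through.** **1. The two periods side by side**

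| | 2007 baseline | Trial |
|---|---|---|
| Source of counts | hospital record | hospital record |
| Study questionnaire and complication items | none | yes, for included patients |
| Cognition and consent requirement | not listed | required |
| Surgery required | not listed | required |
| Structured record-keeping card for nurses | no | intervention wards only |

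The second row can raise recorded events, and the third can lower them. The fourth has no obvious sign. The fifth differs between intervention and control wards, so a control comparison does not remove it.

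**2. The yardstick.** The Power calculation uses a 5-point reduction, SD 10%, alpha 0.05 and power 80%. Two-sided, n = 2 × (1.960 + 0.842)² × (10/5)² = 62.8, so 63 per group. The t-test version gives 63.77, so 64, as stated. The target of 80 equals 64/0.80; the 20% allowance is inferred. The present point changes none of these figures. The 5 points serve only as a scale.

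**3. Illustration of a recording shift.** The documents give neither a complication risk nor the sensitivity of the record, so all inputs here are assumptions. Let p0 be the true risk without the programme, with a true reduction of 0.05. Let s0 be the record's sensitivity in 2007 and s1 its sensitivity in the trial, equal in all wards.

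- Before-after = (p0 − 0.05) × s1 − p0 × s0
- Concurrent = (p0 − 0.05) × s1 − p0 × s1 = −0.05 × s1
- Difference in changes = before-after − p0 × (s1 − s0) = −0.05 × s1

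If s0 = s1 = 0.80, all three equal −4.0 points. With s0 = 0.80 and s1 = 0.90:

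| p0 | Before-after | Control ward's change | Difference in changes | Concurrent |
|---|---|---|---|---|
| 0.30 | −1.5 | +3.0 | −4.5 | −4.5 |
| 0.40 | −0.5 | +4.0 | −4.5 | −4.5 |
| 0.50 | +0.5 | +5.0 | −4.5 | −4.5 |

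The before-after effect moves by 2.5, 3.5 and 4.5 points. The other two contrasts barely move.

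**4. The opposing case-mix shift.** Suppose trial patients have an underlying risk lower by m than the 2007 patients. Before-after becomes (p0 − m − 0.05) × s1 − p0 × s0, so each point of m lowers it by 0.9 points. The recording shift is cancelled at m = 2.5/0.9 = 2.8, 3.5/0.9 = 3.9 and 4.5/0.9 = 5.0 points for p0 = 0.30, 0.40 and 0.50. Beyond that, the comparison flatters the programme. If m is the same in the control ward, the difference in changes and the concurrent contrast both stay at −4.5.

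**5. Precision.** Assume a recorded risk of 0.40 (variance 0.24), full enrolment, no ward effects, and 2007 samples of 300 and 100. The sample sizes follow the criterion of at least 100 hip fracture patients per ward per year.

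- Before-after: √[0.24 × (1/320 + 1/300)] = 3.9 points
- Concurrent: √[0.24 × (1/320 + 1/80)] = 6.1 points
- Difference in changes: √[0.24 × (1/320 + 1/80 + 1/300 + 1/100)] = 8.3 points
- Card yes versus no, randomised: √[0.24 × (1/160 + 1/160)] = 5.5 points

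**The case against.** The strongest reply is that the control group is in the plan. Study design compares the interventions with usual care. The questionnaire is described for included patients generally, so control patients apparently have it too, and a common shift largely cancels. The contrasts among Groups 1-4 are randomised within the same wards and period. All of this stands. It protects those contrasts, but not the stated comparison with 2007.

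A second reply is that the mechanism is indirect. The listed review sources are the medical, nursing and outpatient records plus X-rays, and the limitations section says the method relies on the hospital record alone. The questionnaire is not a listed source. Its nutrition and delirium instruments appear under pre-fracture status, and the pre-discharge items might simply be copied from the chart. This also stands: the questionnaire can raise detection and charting, but nothing shows that it must. The documents are also silent on whether similar screening was routine in 2007.

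A third reply is that an article may leave the modelling of baseline and control to a fuller document. That is fair for model details. The comparison with 2007, however, is stated here and is uncontrolled as stated.

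**Conclusion.** The point holds in limited form. The stated comparison with 2007 mixes the effect with changes in recording, case mix and time, and should not count as evidence of effect. The cognition and consent difference follows directly from the two selection rules. The recording difference is a plausible risk. Size and net direction cannot be derived from the documents; the figures above show only that modest, assumed changes are as large as the 5-point target.

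Three stronger readings are tempting and unsupported.

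- A reader might infer that the trial's own screening biases the result against the programme, or even reverses its sign, as in the last row of the illustration. That row depends on assumed inputs and on no case-mix difference, which could push the other way.
- A reader might infer that the control ward is not used at all. It is, in the concurrent comparison.
- Since ward background information is collected because "This will make it possible to compare the wards and correct for important differences", a reader might infer that adjustment must fail with four wards. That presumes a ward-level regression that the plan does not specify. The Data analysis section plans correction for patient characteristics.

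**What to change.** 1. State that the uncontrolled comparison with 2007 is descriptive and is not evidence of effect.
2. Judge the card by Groups 2 and 4 against 1 and 3, and the leaflet by Groups 3 and 4 against 1 and 2, within the intervention wards.
3. State the programme effect as the intervention wards' change from their own 2007 records minus the control ward's change, adjusted for patient-level covariates. Report it beside the concurrent contrast. First confirm that the control hospital is in the 2007 review; the wording suggests it but does not say so.
4. Restrict the 2007 records, as far as they allow, to patients who would meet the trial criteria. Cognition may be only partly recoverable, and consent not at all.
5. Confirm that trial questionnaires are kept out of the records given to reviewers.

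**Cost.** Mostly wording, plus eligibility coding of the 2007 records. No new data are needed if the control hospital is already covered. The price is precision: on the assumptions above, a standard error of about 8.3 points against 3.9 for before-after and 6.1 for the concurrent contrast. Restricting the 2007 records would widen it further. The result still rests on one non-randomised control ward, and it does not remove recording changes caused by SBAR itself, because the record-keeping side of the card is used only in the intervention wards.

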##### Evaluation

The use of the leaflet will be evaluated by asking the patient about the added value and the usability of the bundles during a short interview by telephone two weeks after discharge. We will consider the leaflet useful if 60% of the patients says they have used the leaflet and found it useful. The effect of the bundles will be evaluated during the telephone interview two weeks after discharge and by measuring avoidable harm (e.g. adverse medication events, urinary tract infections, wound infections, delirium, falls and pressure ulcers) within 6 months after discharge. The patient will be called again around 6 months after discharge to ask about any medical problems occurring after discharge and their recovery in the past six months. Also, the patient records of all included patients will be reviewed by experienced reviewers for additional information about possible complications and avoidable harm after discharge.

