### Outcome measures

The primary outcome measures in this study are the incidence of complications and adverse events, mortality rate within six months after discharge and functional mobility six months after discharge. Secondary outcome measures are length of hospital stay, quality and completeness of information transfer and patient satisfaction with the instruments.

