## Discussion

### Strengths and limitations of the study

One of the strengths of this study is the integrated intervention programme that will be implemented in three surgical wards. All three interventions are aimed at improving a different aspect of the care for elderly hip fracture patients. This approach may have more impact than implementing three separate interventions in different situations and could increase the possibility of finding measurable effects in patient outcomes. The randomisation at patient level reduces the influence of the differences between the three wards. In every participating ward the included patients should be equally distributed over the four intervention groups. Another important aspect of this intervention programme is that it focuses on one specific patient group that will increase in the future. The baseline measurement will give insight into the complications and adverse events that affect this patient group. This information will provide valuable insights and possibilities for improving patient safety. Finally, the follow-up of six months enables us to assess the functional recovery of patients and their experiences during those months. These experiences can be used to improve the care after discharge for this patient group and to explore the possibilities for care that is more adapted to their needs.

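### Functional mobility at six months is a primary outcome, but no score is named for it, so a value comparable with the pre-fracture mobility score is not assured

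*Protocol article*

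**What the plan says.** Outcome measures (and the Abstract) list among the primary outcomes "mortality rate within six months after discharge and functional mobility six months after discharge".

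General data collection and follow up covers measurement in two steps. For the state before the fracture it is specific: "Information about the status before the fracture will be gathered using the 10-item modified Barthel Index for ADL-functioning", together with "the Parker and Palmer pre-fracture mobility score", a nutritional questionnaire and a delirium scale. For follow-up, "two interviews by telephone will be held with all included patients, two weeks and six months after discharge", and in these "patients will be asked some multiple choice questions about their current residence, physical functioning, use of health care" and unexpected events, plus open questions on experiences. No scale is named for either call.

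The Evaluation text for Intervention C adds that the six-month call is made "to ask about any medical problems occurring after discharge and their recovery in the past six months". Strengths and limitations of the study states that "the follow-up of six months enables us to assess the functional recovery of patients".

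Three further points bear on this. Under Blinding, the six-month interviewer does not know the patient's group. Under Study design and Randomisation, patients are randomised among four groups within three intervention wards, while the control group is one ward in another hospital. Under Data analysis, correction for differences in patient characteristics is made only where it is found necessary.

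**The concern.** A primary outcome needs a defined measure before data collection starts. Here the scales are attached to the pre-fracture state, and the six-month value, which is the outcome itself, is described only by question format and topic.

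Items not asked in the call cannot be recovered at analysis, so a later analysis plan cannot repair a wrong choice. If the calls use different items, two things suffer. Recovery in the sense of regaining the pre-fracture level could not be read off one scale. The six-month comparison would also rest on a score whose range and direction the article does not give.

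The comparison with the control hospital is the most exposed. Those patients are not randomised against the others, so pre-fracture mobility may differ between them and the intervention patients.

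**Working it through.** **1. What is fixed for each primary outcome in the article.**

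| Primary outcome | Measure stated | Where |
|---|---|---|
| Complications | National complication registration; structured record review | Data analysis; Baseline measurement |
| Adverse events | Three criteria; six-point causation scale, scores 4-6 count | Data analysis |
| Mortality within six months | Needs no scale | Outcome measures |
| Functional mobility at six months | None named | – |

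Mobility is the only primary outcome that needs a measure and has none.

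**2. Could another source supply it?** The second record review looks for complications, adverse events, quality of record keeping and transfer information. Mobility is not on that list. As described, the six-month call is the only source.

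**3. Does any section say the scales are repeated, or are not repeated?** Neither. The mobility score and the ADL index appear only in the sentence on pre-fracture status. The descriptions of the calls mention physical functioning and recovery without a scale. The supportable reading is therefore that comparability is not assured.

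**4. What the baseline score is needed for.** Write Y for six-month mobility, X for the pre-fracture score and b for the slope of Y on X.
- Intervention versus control (not randomised): the unadjusted difference in mean Y contains b × (difference in mean X). Adjusting for X removes that term. Other differences between hospitals remain.
- Among the four randomised groups: the expected difference in mean X is zero. With r the correlation of X and Y, adjustment reduces the residual variance by a factor of about 1 − r².
- Neither use strictly requires X and Y to share a scale. Return to the pre-fracture level does.

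**5. The plan's own sample size.** The Power calculation gives 64 per group for complications, from a difference of 5 and an SD of 10. Two-sided alpha is assumed, since sidedness is not stated.
- Normal approximation: n = 2 × (1.960 + 0.842)² × (10/5)² = 62.8, so 63.
- The t-test version gives 63.77, so 64. The figure reproduces.
- 64 / (1 − 0.20) = 80, so recruiting 80 corresponds to a 20% loss.
- All groups: 320 + 80 = 400 patients.

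This calculation is not about mobility, and no mobility effect or SD is given. For orientation only, the detectable standardised difference at 80% power is (1.960 + 0.842) × √(2/n): 0.50 for n = 64 and 0.44 for n = 80, whatever scale is used.

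**6. Deaths before the call.** The Background gives only one-year mortality, 14 to 36%, and the trial excludes patients who are not in good cognitive condition. If six-month mortality were 5 to 20% (an assumption), then 0.05 × 80 = 4 to 0.20 × 80 = 16 patients per group would have no mobility value because they died.

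**The case against.** The strongest reply is that this is a condensed article and that follow-up questionnaire content belongs in the full protocol. Multiple choice describes a format, and the items of the named scales could be asked in that format. This stands in part. A reader might infer that recovery cannot be scored on one scale, that it could be computed for no patient, or that the six-month items are improvised or unvalidated. The article supports none of these; it is silent on where the items come from and how they are scored.

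Second, the outcome is defined as a level at six months, not as a change from the pre-fracture state. A comparison between groups at six months needs a defined score, but not the baseline scale. That is correct. It limits the harm of differing scales but leaves the need for a defined score. The Discussion does not define functional recovery, so equating it with return to the pre-fracture level is an interpretation.

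Third, handling of deaths is commonly left to the analysis plan. Mortality is itself a primary outcome and would be reported beside mobility, and the article does not announce an analysis of survivors only. A reader might infer that the mobility result will be biased by death in a known direction. The documents do not support that, and the 4 to 16 deaths per group rest on an assumed rate.

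What the reply does not answer is that the article names four instruments in the same section and gives scoring rules for adverse events, yet names nothing for this primary outcome.

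**Conclusion.** The point holds in limited form. The article does not state which score measures functional mobility at six months, or whether the pre-fracture score is repeated, so a comparable six-month score is not assured. It affects one primary outcome in all five groups, and most of all the comparison with the non-randomised control hospital, where adjustment for pre-fracture mobility should not depend on a later judgement of need.

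No bias or loss of power can be quantified from the document. The conclusion rests on the article's text alone and assumes that no unshown full protocol already fixes the instrument. If one does, the remedy for measurement is one sentence in the article. The change should be made before the six-month calls begin, and it does not touch the sample size.

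**What to change.** - **General data collection and follow up:** state that the mobility score used for pre-fracture status is asked again in the six-month call, with the same items and scoring, and that the ADL index is asked as support. The interviewer for that call is already planned to be unaware of group.
- **Outcome measures:** define the primary mobility outcome as that score at six months.
- **Data analysis:** adjust the mobility comparison for the pre-fracture score in every comparison, including that with the control hospital, in place of adjustment only where judged necessary.
- **Deaths:** state how patients who die before the call enter the mobility analysis. Ranking them below the lowest score is one option among several and is not required here.

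The cost is a few more minutes in a call already planned, and some changes of wording. The drawback is a slightly longer interview for elderly patients.
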